**Figure 1 F1:**
[figure not shown]
**Consort diagram**.

### Interventions

#### Maintenance antidepressants (m-ADM)

As part of the inclusion criteria, patients eligible to take part must be receiving treatment with antidepressant medication in line with the BNF and 2009 NICE guidelines. The m-ADM relapse/recurrence prevention intervention will be an extension of the ADM treatment that is an inclusion criterion for the study. In the UK almost all ADM prescriptions are issued by GPs [32]. Therefore GPs will be responsible for patients' ADM treatment in line with NICE guidelines and contemporary best practice [11]. NICE recommends that patients be maintained on ADM for 2 years after achieving remission, and then should only be tapered in accordance with the NICE guidance for recurrent depression. The guideline recommends that factors such as age, co-morbidity and other risk factors should inform the use of longer-term m-ADM. In the exploratory trial, at study entry the mean time on m-ADM was 340 days, with a significant distribution of patients who had been taking m-ADM for many years. The NICE guidance also speaks to monitoring, ADM type, dose, switching and augmentation.

Medication adherence will be monitored through patients' self-report using the Adult Service Use Schedule (AD-SUS) [33] and the Morisky Medication Adherence Instrument [34] and through manual checks of the GP practice databases at 12 and 24 month follow-ups. We will encourage patients to adhere to medication for the full length of the trial by writing to both the patient and their GP explaining that they have been randomised to maintenance antidepressants and asking them to continue to take a therapeutic level of antidepressants for the 2-year duration of the trial.

***Mindfulness-based Cognitive Therapy (MBCT, see ***http://www.mbct.co.uk**) **is an 8-week, group based programme (12-15 patients per group), designed to teach skills that prevent depressive relapse/recurrence. It is a fully manualised psychosocial intervention with the treatment rationale for each session outlined in full [17]. It is derived both from mindfulness-based stress reduction, a programme with demonstrated efficacy in ameliorating distress in people suffering chronic disease [35], and from cognitive-behavioural therapy for acute depression [36], a programme with demonstrated efficacy in preventing depressive relapse/recurrence [37]. MBCT is based on theoretical and empirical work showing that depressive relapse is associated with the reinstatement of automatic modes of thinking, feeling and behaving that are counter-productive in contributing to and maintaining depressive relapse and recurrence (e.g., self-critical thinking and behavioural avoidance) [38]. Participants learn to recognize these "automatic pilot" modes and to deal with them in more functional ways by employing complementary cognitive-behavioural and mindfulness techniques. The cognitive-behavioural component involves responding to negative thinking and behavioural activation. In the latter stages of the course patients develop an "action plan" that sets out strategies for responding when they become aware of early warning signs of relapse/recurrence. The mindfulness component involves extensive rehearsal of mindfulness skills (e.g., meditation practice) designed to improve patients' attentional control, ability to decentre from negative thinking, and emotion regulation. Session content includes psycho-education, teaching/discussion of key cognitive-behavioural skills, guided mindfulness practices, review of weekly homework (40 minutes of mindfulness practice per day and generalisation of cognitive-behavioural skills). MBCT is an accessible and acceptable treatment as evidenced by low attrition in trials and experience in a range of clinical settings.

The MBCT therapists will be mental health professionals with extensive training in MBCT. All therapists will be judged as ready to instruct MBCT classes by an MBCT expert external to the trial prior to starting the trial groups. During the trial, therapists will receive weekly supervision from an experienced MBCT therapist with the requisite skills to supervise MBCT.

In our exploratory trial we developed a model for offering MBCT in primary care settings to groups of up to 15 patients, with built in checks on accessibility/acceptability, therapist adherence, and competence. Eighty-five per cent of people randomised to MBCT participated in ≥4 sessions and mean ratings of MBCT acceptability were high. Levels of MBCT instructor competence and adherence in the exploratory trial were judged to be at or above acceptable levels by an MBCT therapist independent of the trial [25]. An MBCT therapist independent of the trial will provide checks on adherence/competence based on video-taped MBCT sessions. Adherence will be assessed using the Mindfulness-based Cognitive Therapy Adherence Scale [MBCT-AS; [39]]. The MBCT-AS scale is a 17-item measure of observable therapist behaviours (rated 0, *no evidence*; 1, *slight evidence*; 2 *definite evidence*; range of scores 0-34).

##### ADM tapering in the MBCT arm: Rationale and protocol

The rationale for this trial is the development of a psychosocial intervention for the prevention of depressive relapse/recurrence that provides an *alternative *to the current treatment of choice, m-ADM. Consequently, once patients in the MBCT arm of the trial have learned skills for preventing relapse/recurrence, they will be invited to taper ADM with GP support. A protocol for ADM tapering was developed in the exploratory trial in accordance with NICE guidance regarding information provided to the patient, time course, monitoring of discontinuation/withdrawal symptoms, and consideration of the drugs half-life. In the exploratory trial over the follow-up period (*circa *450 days), the mean number of days on ADM was significantly different across the two groups: m-ADM, M = 411.4 > MBCT, M = 266.46; t = 5.40, *p *< 0.0001. Six months after the end of MBCT 75% of the patients in the MBCT arm of the trial had successfully discontinued their medication. These data testify to the relative success of the tapering/discontinuation regime established in the exploratory trial. However, they also highlight the pragmatic reality that some GPs and/or patients will choose not to taper and we have therefore introduced ADM use as a secondary outcome and the analysis plan will examine this variable in the primary and secondary analyses. We will encourage patients to discontinue their medication within 6 months of the end of their MBCT group.

The MBCT manual has been adapted to include more work on developing a relapse signature and response plan that explicitly includes discontinuation/resumption of ADM. If patients in the MBCT arm experience a significant deterioration following tapering, they will be encouraged to use the skills they learned in MBCT.

### Sample size

Different relapse prevention interventions with different populations produce different absolute rates of depressive relapse/recurrence. Therefore, we have based our sample size on estimated hazard ratios for MBCT *vs*. m-ADM rather than estimated absolute relapse/recurrence rates. We canvassed service users and clinicians who concurred that a relative reduction in relapse/recurrence of 10% would be clinically important. ***(i) The policy question: ***The systematic review of MBCT *vs*. usual care for patients with recurrent depression reports hazard ratios of .47 and .28 for the key trials [24]. We applied several conservative assumptions (first row of Table 1). First, even though the exploratory trial data suggest that the hazard ratio was improving in favour of MBCT as the length of follow-up increased [25], we assumed the hazard ratio of .63 at 15 months to power the proposed trial at 24-months follow up. Second even though attrition from MBCT trials to date is consistently <15%, we have assumed an attrition rate of 20% over the 24-months of follow-up. Finally, we assumed there may be a small clustering effect (ICC = 0.01). The resultant sample size calculation assumptions and output are shown in Table 1 based on 80% power and significance set at .05. This leads to a total sample size of 420 across the two groups.

**Table 1 T1:** Sample size calculation

Author	Comparison	Mean hazard ratio	ICC	Design factor**	Attrition rate	**Sample size per group**^**a**^
Conservative scenario	MBCT *vs*. m-ADM	0.63	.01	1.11	20%	210

Kuyken et al., 2008 [25]	MBCT *vs*. m-ADM	0.63	-0.02	1.0	7%^a^	160

Ma & Teasdale, 2004 [22]	MBCT *vs*. usual care	0.28	-0.008	1.0	3%^b^	14^c^

Teasdale et al., 2000 [23]	MBCT *vs*. usual care	0.47	-0.04	1.0	5%^b^	41^c^

Sample size necessary for 90% power at 5% significance at 24 months;

^a ^at 15 months; ^b ^at 60 weeks, ^c^assuming exponential survival function.

Note group size of 12

***For the secondary outcomes***, meta-analyses of generic mindfulness approaches suggest medium effect sizes in changes in depressive symptoms [19,40] and our exploratory trial suggests medium effect sizes for the secondary outcomes of residual depressive symptoms, psychiatric co-morbidity and quality of life [25]. The sample size estimate for our policy question will enable us to detect a medium between-groups effect size (standardised mean difference or Cohen's d = 0.40) on the main secondary outcomes.

### Proposed outcome measures

The primary outcome in depression relapse prevention studies is sustained remission (i.e., freedom from relapse/recurrence). In addition, patients, health care professionals and NHS policy makers value other outcomes including quality of life, depression free days and co-morbidities. There was preliminary evidence from our exploratory trial that MBCT may prove to be superior to m-ADM on these primary and secondary outcomes.

#### Primary outcome

The occurrence of any depressive relapse/recurrence, and time from randomisation to relapse/recurrence, will be assessed using the Longitudinal Interval Follow-up Evaluation, a form of the Structured Clinical Interview for DSM-IV (SCID) [41,42] designed for longitudinal studies of depression. A patient will be judged to have had a relapse/recurrence if s/he was diagnosed as having a major depressive episode (a score of 5 for 2 consecutive weeks) at any time during the 24-month follow-up period.

#### Secondary outcomes

A unique aspect of our trial is the inclusion of a range of secondary outcome measures including those highly valued by patients themselves. Residual depressive symptoms will be assessed with the observer-rated interviewer administered 17-item HRSD [43] and a well established self-report measure, the [Beck Depression Inventory, 2nd edition; [44]]. Psychiatric co-morbidity will be assessed with the full SCID, and medical co-morbidities with a screening questionnaire. Depression free days will be calculated from the SCID. Quality of life will be assessed with the EQ-5D health-related quality of life measure [45,46].

#### Process data

Our explanatory question asks "is an increase in mindfulness skills the key mechanism of change of MBCT?" We address this via embedded quantitative and qualitative process-outcome studies across the trial arms. Quantitative measures will be administered at baseline and again one month after the end of the MBCT (or the equivalent time point in the m-ADM arm) so that change scores can be used to predict treatment outcome at the different follow ups using mediational analyses [28]. Critically, this design ensures that changes in putative mediators temporally precede the primary outcome (relapse/recurrence), a prerequisite in inferring mediation, and allows baseline-to-post-treatment change in symptoms to be statistically controlled. The same measures will be administered at study end to assess stability of change. We will also use experience sampling methods on sub-samples at study end to test emerging models of emotion regulation post-MBCT. All these assessments will comprise validated questionnaire and cognitive-experimental measures of the variables that we hypothesise mediate MBCT's effects.

In addition, qualitative data will be collected via semi-structured interviews and written responses to access patients' own accounts of the mechanisms and impacts of treatment. At the end of treatment (or the equivalent time point in the m-ADM arm), all participants will write short accounts of their experiences of and perceived impacts of treatment in response to open-ended questions. We will collect similar data from all participants at the end of the trial in order to gain a broad understanding of the impacts of both MBCT and ADM tapering and m-ADM over the follow-up period. Additionally at trial end, semi-structured interviews designed to obtain a more in-depth understand of the ongoing mechanisms and impact of treatment over the follow-up period will be conducted with sub-samples. Interviews will focus on the patients' views of the role of mindfulness, strategies to prevent or cope with relapses, and broader impacts of treatment in patients' lives, and will be informed by previous work on experiences of MBCT [26]. Integration with the quantitative process data will enhance understanding of change mechanisms that can improve MBCT's potential efficacy.

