### Setting, participants, recruitment and randomization

Four hundred and twenty patients will be recruited through primary care and treated in accessible primary care or community settings. Inclusion and exclusion criteria were refined through the exploratory trial to maximise real world applicability to the population of people in primary care with recurrent depression who are treated with ADM and who are interested in considering a psychological approach to relapse/recurrence prevention. Inclusion criteria are: a diagnosis of recurrent major depressive disorder in full or partial remission according to the DSM-IV, with 3 or more previous major depressive episodes; aged 18 or older; and on a therapeutic dose of ADM in line with the British National Formulary (BNF) and NICE guidance [11]. Currently MBCT is indicated only for more recurrent depression (3 or more episodes) based on the initial trial and its procedural replication [24]. To meet inclusion criteria the participant must have experienced three previous episodes where depression is the primary disorder and not secondary to substance abuse or bereavement. Exclusion criteria are: patients who are currently depressed, co-morbid diagnoses of current substance abuse (patients with previous substance abuse are eligible for inclusion as long as they are in sustained full remission); organic brain damage; current/past psychosis, including bipolar disorder; persistent antisocial behaviour; persistent self-injury requiring clinical management/therapy; and formal concurrent psychotherapy. We include older adults with depression on the basis of the high prevalence of depression in older adults and a promising pilot study of MBCT with this group [29].

The exploratory trial developed a recruitment methodology that proved acceptable and effective [30]. In each of the four localities (Bristol, Exeter, Plymouth/South Devon and North Devon) and five compact 'time slices' that coincide with MBCT group times, research staff will recruit participants meeting inclusion and exclusion criteria, attempting to ensure that baselines assessments occur as closely as possible, normally within one month, to the start of the next MBCT group.

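### The protocol says its design guarantees that mediator change precedes relapse, but relapses count from randomisation and the mediators are re-measured about 2.8 to 3.8 months after baseline

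*Protocol article*

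**What the plan says.** The Process data section of the protocol article plans to use change scores in the putative mediators to predict outcome. The measures are "administered at baseline and again one month after the end of the MBCT", or at the equivalent time in the m-ADM arm. The section then claims that "this design ensures that changes in putative mediators temporally precede the primary outcome (relapse/recurrence), a prerequisite in inferring mediation". The same sentence adds that symptom change from baseline to post-treatment can be controlled statistically.

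The Primary outcome section defines the outcome as "The occurrence of any depressive relapse/recurrence, and time from randomisation to relapse/recurrence", and a major depressive episode counts if it occurs "at any time during the 24-month follow-up period". No early period is set aside.

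Three places fix the timing of the second mediator measurement:
- Setting, participants, recruitment and randomization: baseline assessments are to fall close to group start, "normally within one month, to the start of the next MBCT group".
- Interventions: the MBCT course lasts eight weeks.
- Process data: re-measurement comes one month after the course ends.

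The Statistical analysis plan section, part (ii)(b), describes mediation analyses of pre- to post-treatment change across the arms. It does not alter the time origin of the outcome.

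**The concern.** A change score exists only once its second measurement has been taken. If a patient relapses before then, the outcome event comes first and the supposed cause is completed second. The score may then partly reflect the relapse. A relapse that worsens the mediator would create an association between poor mediator change and relapse even if the mediator did nothing. That error would favour the hypothesis under test, that gains in mindfulness skills are the key mechanism.

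The article itself calls temporal order a prerequisite for inferring mediation, and it treats the order as already secured by the design. An analyst relying on that sentence would see no need to handle early relapses separately.

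**Working it through.** **What the article computes.** It gives no figure for relapses before re-measurement, so there is nothing on this point to reproduce. Its one computed figure, 210 per group, is roughly recovered from 60% against 1 − 0.40^0.63 = 43.9% at 80% power: 150 × 1.11 / 0.80 = 208. It says nothing about early timing and is not used below.

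**Step 1: length of the window.**
- Eight weeks = 56 / 30.44 = 1.84 months.
- Shortest: 1.84 + 1 = 2.84 months, with the group starting at once.
- Longest in the normal case: 1 + 1.84 + 1 = 3.84 months.

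The one-month wait runs from the baseline assessment, so the interval from randomisation may be slightly under 3.84. It should not fall below 2.84, because allocation has to precede the group.

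**Step 2: does the order hold?** Relapses count from month 0 and the change score is complete at month 2.84 to 3.84. Any relapse in between breaks the claimed order, whatever the relapse rate. Excluding currently depressed patients at entry places only the baseline measurement before relapse, not the change.

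**Step 3: how many relapses could be affected?** Inputs are the exploratory trial's 15-month rates given in the Background: m-ADM 60%, MBCT 47%. With constant hazard in each arm, F(t) = 1 − (1 − p15)^(t/15). The pooled share for equal arms is the sum of F(t) over arms divided by the sum of F(24).

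| | m-ADM | MBCT | Pooled share of 24-month relapses |
|---|---|---|---|
| F(2.84) | 15.9% | 11.3% | 27.2 / 140.7 = 19.4% |
| F(3.84) | 20.9% | 15.0% | 35.9 / 140.7 = 25.5% |
| F(24) | 76.9% | 63.8% | |

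In 420 patients before attrition, this is about 57 to 75 of 295 relapses.

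**Step 4: sensitivity to the assumptions.** A lower overall risk matters little. With 50% relapsing by 24 months, F(t) = 1 − 0.5^(t/24), and the share is 7.9/50 = 16% to 10.5/50 = 21%. The shape of the hazard matters much more. With a Weibull form tied to the same 15-month rates, F(t) = 1 − (1 − p15)^((t/15)^k):

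| Shape k | Share at 2.84 months | Share at 3.84 months |
|---|---|---|
| 0.75 (falling hazard) | 30% | 37% |
| 1 (constant) | 19% | 26% |
| 1.25 | 12% | 18% |
| 1.5 | 8% | 12% |
| 2 (strongly rising) | 3% | 6% |

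The share varies widely but is above zero in every case.

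**The case against.** **Symptom change is to be controlled.** This is the strongest reply, because it targets the route by which an early relapse would distort the mediator score. A simulation illustrates it: 336 patients (420 × 0.80), a mediator with no effect, a Cox model from randomisation, re-measurement at 3.84 months and constant hazard. If an early relapse worsens the mediator by 0.3 to 0.5 SD, the mediator is falsely significant in roughly 17% to 44% of trials without symptom control. With symptom change in the model, and with relapse acting on the mediator only through symptoms, the rate is about 6%.

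A reader might therefore infer that the planned analysis has a high false-positive rate. The documents do not support that. The high figures describe an analysis without the stated control, and the 0.3 to 0.5 SD drop has no source in the article. What remains is narrower. Control is incomplete if a patient relapses and recovers before the assessment, or if relapse affects the mediator outside the measured symptoms. Nor can adjustment put the measurements in the order the sentence claims.

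**Early hazard may be low.** Patients enter in full or partial remission on a therapeutic dose, and MBCT patients are invited to taper only after learning the skills. This is fair, and it is why a fifth to a quarter should not be read as an established share. The article gives no early relapse timing.

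**The full analysis plan may restart the clock.** It may, and the article's silence on that detail is not the complaint. A restart elsewhere would still leave the printed sentence wrong.

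**A landmark analysis has its own bias.** This stands, and the fix below has to say so.

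**Conclusion.** The claim that the design *ensures* the order is wrong as written. This follows from the article's own outcome definition and assessment schedule and needs no assumption about relapse rates.

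The size is an estimate: about 19% to 26% of 24-month relapses under constant hazard, and about 3% to 37% over Weibull shapes 2 to 0.75. It assumes that the exploratory trial's rates carry over to 24 months, that randomisation is close to baseline, and that the lower MBCT rate applies from month 0, before the course has been delivered.

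The point concerns the explanatory question only. A reader might go further and infer that the policy comparison is compromised or that any mediation result would be spurious. Neither follows. The primary analysis does not use the mediators. Some real mediator change may also precede an early relapse; the measured score simply cannot show that it did.

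**What to change.** 1. In Process data, replace the guarantee with a statement that the order holds only for relapses after the post-treatment assessment.
2. For the mediation analyses, start the relapse clock at that assessment (or the equivalent time in the m-ADM arm). Include participants still relapse-free at that point, and keep the planned adjustment for symptom change.
3. State that this set is selected after randomisation, possibly differently by arm, so its results are conditional on being relapse-free at the landmark and the comparison of arms within it is no longer purely randomised. Under constant hazard, 79% to 84% of m-ADM and 85% to 89% of MBCT patients would remain.
4. An analysis from randomisation can be kept as a sensitivity analysis.

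**Cost.** Wording only: no new visits, data or patients. Some precision is lost. Under constant hazard about 295 − 75 = 220 to 295 − 57 = 238 relapses remain before attrition. If variance scales with the inverse of the number of events, standard errors rise by √(295/238) = 1.11 to √(295/220) = 1.16 times. The intention-to-treat primary analysis stays as planned, from randomisation.

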### Our exploratory trial

In our exploratory trial 123 patients with recurrent depression on m-ADM were randomised to either continued m-ADM or MBCT plus m-ADM tapering/discontinuation [25]. The findings suggest that MBCT may not only provide an alternative to m-ADM (relapses at 15 months: MBCT 47% *vs*. m-ADM 60%), but that in an adequately powered definitive phase III trial it may produce superior outcomes. The study suggested that MBCT was also superior to m-ADM in terms of improved quality of life, reduced residual depressive symptoms, and reduced psychiatric co-morbidity. Finally, a secondary qualitative study suggested several putative mechanisms of action [26].

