#### (ii) The explanatory questions

These will be examined using a mix of three mutually informative methods:

(a) For the MBCT arm time to relapse/recurrence of depression will be compared using Cox regression proportional hazard survival analysis, allowing for the stratification variables and any group differences in ADM tapering/usage (if rates of tapering/usage are different across the two arms).

(b) Mediational analyses will investigate hypothesised mechanisms of change pre-/post-treatment across the trial arms using approaches to testing mediation that allow multiple mediators in one model using the approach set out by Kraemer et al. (2002) and as used in our exploratory trial [49].

(c) Qualitative data will be analysed using thematic analysis (with NVivo software). This will combine inductive and deductive approaches and will be conducted collaboratively by a small sub-group of the research team in order to enhance validity.

The Data Monitoring and Safety Committee will oversee analysis at 3 and 12 months for patient safety and at 12 and 24 months for the primary outcome analyses. Given the public health importance of the findings we anticipate disseminating the findings at 12 and 24 month follow-ups as soon as they are available.

(d) Differences in mean costs will be analysed using standard parametric t-tests with the validity of results confirmed using bias-corrected, nonparametric bootstrapping (repeat re-sampling) [50]. Despite the skewed nature of cost data, this approach is recommended to enable inferences to be made about the arithmetic mean [51]. The primary economic analysis will focus on the policy question: MBCT vs. mADM. Cost-effectiveness will be assessed through the calculation of incremental cost-effectiveness ratios (ICER) and will be explored in terms of relapse/recurrence and quality adjusted life years using the EQ-5D measure of health-related quality of life. Uncertainty around the cost and effectiveness estimates will be represented by cost-effectiveness acceptability curves [52].

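### Symptom change offered as a control in the mediation analysis covers the same interval as mindfulness change and is expected to respond to MBCT, so the mindfulness path needs reporting both with and without it

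*Protocol article*

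**What the plan says.** The Process data section poses the explanatory question: "is an increase in mindfulness skills the key mechanism of change of MBCT". On timing it states: "Quantitative measures will be administered at baseline and again one month after the end of the MBCT", with an equivalent point in the m-ADM arm. It claims two advantages for this schedule. The first concerns order in time: "this design ensures that changes in putative mediators temporally precede the primary outcome (relapse/recurrence". The second is that the schedule "allows baseline-to-post-treatment change in symptoms to be statistically controlled".

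Elsewhere, the article expects MBCT to move symptoms. The account of the exploratory trial says the study suggested that MBCT was "superior to m-ADM in terms of improved quality of life, reduced residual depressive symptoms, and reduced psychiatric co-morbidity". The Sample size section adds that "our exploratory trial suggests medium effect sizes for the secondary outcomes of residual depressive symptoms, psychiatric co-morbidity and quality of life", and says the trial can detect a standardised difference of 0.40 on the main secondary outcomes. Residual symptoms are listed among those outcomes, without a visit schedule.

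The analysis section, under (ii)(b), specifies "approaches to testing mediation that allow multiple mediators in one model". It does not name symptom change as a covariate or as a mediator. The rule at the head of the Statistical analysis plan, that models are run with and without adjustment, applies to baseline characteristics only.

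**The concern.** A baseline-to-post-treatment change in symptoms is a post-randomisation variable. Since MBCT is expected to affect it, it may be a step on the route from mindfulness to relapse. Conditioning on such a step leaves only the part of the mindfulness effect that bypasses symptoms, which is narrower than the question asked.

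The temporal argument does not help. It places mediator change before relapse but gives no order between mindfulness change and symptom change. The opposite order is also plausible: better mood may raise mindfulness scores and lower relapse risk, in which case omitting symptom change produces a mindfulness path that is not real.

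At stake is the answer to one of the trial's two stated research questions. A mechanism that works by lowering residual symptoms could be reported as weak or absent, or improved mood could be reported as a mindfulness mechanism.

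**Working it through.** The article gives no effect size, power or sample size for the mediation analysis, so there is no figure to reproduce. The paths below are assumptions that show direction and range.

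**Notation.** T = arm, M = mindfulness change, S = symptom change, Y = outcome. Indirect effect through mindfulness = (T→M) × (coefficient of M in the outcome model).

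**Case A: symptoms downstream of mindfulness.** Assumed: T→M = 0.4, total M→Y = -0.3, M→S = -0.5. True indirect effect = 0.4 × (-0.3) = -0.12. Let p be the share of M→Y that runs through S. With S in the outcome model, the coefficient of M is -0.3 × (1 - p), so the indirect effect is -0.12 × (1 - p).

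| p | without S | with S | removed |
|---|---|---|---|
| 0 | -0.12 | -0.12 | 0% |
| 0.25 | -0.12 | -0.09 | 25% |
| 0.50 | -0.12 | -0.06 | 50% |
| 0.75 | -0.12 | -0.03 | 75% |
| 1.00 | -0.12 | 0.00 | 100% |

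A simulation of 400,000 patients agreed with every cell to within 0.002.

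**Case B: symptoms upstream, mindfulness inert.** Assumed: T→S = -0.4, S→M = -0.5, S→Y = c, residual variances 1. True indirect effect through M = 0. Then T→M = (-0.4) × (-0.5) = 0.2. Without S, the coefficient of M is c × (-0.5)/(0.25 + 1) = -0.4c, so the false indirect effect is 0.2 × (-0.4c) = -0.08c:
- c = 0.2: -0.016
- c = 0.3: -0.024
- c = 0.5: -0.040

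With S in the model the estimate is 0. The simulation gave the same values.

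**Time-to-event version.** Cox fits on 60,000 simulated patients, with an assumed 61% relapse (the article gives 47% and 60% at 15 months in the exploratory trial). Log hazard ratio per SD of mindfulness:

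| Assumed structure | without S | with S |
|---|---|---|
| M direct -0.15, M→S -0.4, S→relapse 0.4 (share through S = 0.16/0.31 = 52%) | -0.296 | -0.150 |
| M direct 0, M→S -0.5, S→relapse 0.5 (all through S) | -0.233 | 0.001 |
| S→M -0.4, M inert, S→relapse 0.5 | -0.185 | 0.002 |

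**Counting the path through symptoms.** In Case A with p = 0.5, S→Y = 0.5 × 0.3/0.5 = 0.3. Direct part: 0.4 × (-0.15) = -0.06. Path through symptoms: 0.4 × (-0.5) × 0.3 = -0.06. The sum is -0.12, the true effect.

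The same sum in Case B with c = 0.3, wrongly assuming that M precedes S, gives 0 + 0.2 × (-0.4) × 0.3 = -0.024, the false path. Counting the path through symptoms is therefore right under one ordering and wrong under the other, and the data cannot tell which holds.

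**The case against.** The strongest objection is that the article fixes no such model. Process data describes what the schedule makes possible, and (ii)(b) names no symptom covariate and permits several mediators in one model. The covariate list could properly be left to a fuller document. This stands: a reader might infer that symptom change is fixed as a covariate, and the text does not say so. What remains is that the article promotes this control as an advantage without stating the causal role it assumes.

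Secondly, controlling for concurrent mood is a recognised check that mindfulness change is more than feeling better, and in Case B it gives the right answer. This also stands. It supports reporting both models, not dropping the control.

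Four further inferences are not supported:
- That symptoms and mindfulness are measured at the same visit. Only a shared baseline-to-post-treatment interval is stated.
- That the intention-to-treat effect would be altered. Nothing puts symptom change into the primary Cox model, which contains treatment and the stratification variables.
- That renaming symptom change a parallel second mediator cures the problem. The outcome model would still contain arm, mindfulness and symptoms, so the mindfulness coefficient would be identical.
- That the two models bracket the truth. This holds for the structures simulated; unmeasured common causes of symptoms and relapse would break it.

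**Conclusion.** The point holds in a limited form. The article offers, as a strength, control for a variable that changes over the same interval as the mediator and that it expects treatment to affect. With that control, the mindfulness path is only the part not passing through symptoms; without it, the path may include confounding by mood.

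Under the assumed paths, the control removes 0 to 100% of a true indirect effect. Omission creates a false one of -0.016 to -0.040 on the linear scale, or -0.185 per SD on the log hazard scale in the Cox illustration. These sizes rest wholly on assumed paths. A reader might infer that the mechanism conclusion is bound to reverse. It vanishes only when the whole effect runs through symptoms; at about half, the Cox coefficient falls from -0.296 to -0.150 and is still present.

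Only the explanatory mediation analysis is affected.

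**What to change.** State in Process data and in (ii)(b) that:

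1. Mediation models adjust for baseline symptoms. This needs saying because the general rule selects covariates by comparing the arms at baseline. Randomisation stratified on symptom status makes an imbalance there less likely, yet baseline symptoms can still confound mindfulness and relapse.
2. The mindfulness path is reported both without and with post-treatment symptom change.
3. The figure with symptom change is labelled as the part of the mindfulness effect not passing through symptoms.
4. Any path from mindfulness through symptoms to relapse counts as part of the mindfulness mechanism and is not discarded. The ordering this assumes is stated, with a note that one shared post-treatment interval cannot verify it.

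No rule should require the path to hold in both models before mindfulness is called the key mechanism. That would reject a mechanism acting wholly through symptoms (0.001 with symptom change in the Cox illustration, although the mechanism is real).

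The cost is one extra model on data already planned, two figures where a reader might want one, and a more cautious mechanism claim.
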